
### Measurement time points

The data collection is summarised in table 1.

**Table 1 T1:** Data and measurement time points

Informant	Instrument	No. of items	Measurement points
Patient	BDI-II	21	Screening, BA, after the fifth therapy session, Post, FUP 1, 2, 3
	SCID-5-SPQ	106	Screening
	GAD-7	7	BA, Post, FUP 1, 2, 3
	PHQ-15	15	BA, Post, FUP 1, 2, 3
	OPD-SQS	12	BA, Post, FUP 1, 2, 3
	IIP-32	64	BA, Post, FUP 1, 2, 3
	WHOQOL-BREF	16	BA, Post, FUP 1, 2, 3
	PATHEV	11	BA
	Basic characteristics	app. 40	BA
	WAI-SR	12	After every session
	PSQ-Mod	3	After every session
	MOCPI	22	After every session
	Symptom severity VAS	1	After every session
	additional treatments	3	After every session
	INEP	21	Post, FUP 1, 2, 3
Observer interviews and ratings	SCID-5-CV	Adaptive	Screening
	SCID-5-PD	Adaptive	Screening or BA (depending on interview duration)
	adapted CSSRI	Adaptive	Screening, Post, FUP 1, 2, 3
	CSSR-S	23	Screening
	GRID-HAM-D-21	21	BA, Post, FUP 1, 2, 3
	Dropout-Interview	3	Flexibly
	BIFS-AFT	12	One session each of session 1-4/5-10, 11–16, 17–20 (if available)
	PIL	37	Sessions selected based on process data
	Empathy Scale	10	Sessions selected based on process data
	CCSS-S	14	Sessions selected based on process data
	IMI-R	64	Sessions selected based on process data
	3RS	22	Sessions selected based on process data
	FIS	6*9	BA, FUP1
Therapist	Basic characteristics, experience, practice	40	BA, Post, FUP 1, 2, 3
	Skills Change Index	10	BA, Post, FUP 1, 2, 3
	Relational Manner	35	BA, Post, FUP 1, 2, 3
	ERQ	10	BA, Post, FUP 1, 2, 3
	TAS-20	20	BA, Post, FUP 1, 2, 3
	FDEB	30	BA
	BFI-10	10	BA
	ISC-G	40	BA
	IIP-32	32	BA
	CAMSQ	20	BA
	SANB	5	BA
	FIS self-rating	9	BA, FUP 1
	CSQ-8-mod	8	Post, FUP 1, 2, 3
	WAI-SR	12	After every session
	PSQ-Mod	3	After every session
	Report on important events	Adaptive	flexibly
	Relational manner – state	35	After the fifth session
Supervisor	Basic characteristics, experience, practice	app. 10	BA
	Attendance sheet	4-5	After every supervision

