### Statistical analyses

Results are reported according to the Consolidated Standards of Reporting Trials (CONSORT) statement.^124^ Analyses are carried out with standard software: SPSS, V.29 or newer (IBM), SAS, V.9.4 or newer (SAS Institute), or R (V.4.3.3). A statistical analysis plan that contains the details of all planned analyses will be finalised before database lock.

Descriptive data are presented overall and separated by randomised group. As descriptive statistics, mean, SD, median, first and third quartile or minimum and maximum are calculated for continuous variables. For categorical variables, absolute and relative frequencies are reported.

First primary outcome (hypothesis I): We use a linear mixed model with repeated measures with changes from baseline as dependent variable, IG, therapeutic approach (CBT vs PDT), time and comorbid SCID5 personality disorder (yes vs no) as fixed effects, baseline BDI-II score as covariate, time by IG interaction, and cooperation centre, supervision group (if possible), therapist (=cluster) and patient as nested random effects. The interaction term is eliminated from the model if the corresponding interaction p value is >0.15. Measurement points up to and including the first follow-up (within the current funding period) will be considered. The contrast of the IG after 20 weeks is the result of the primary analysis. This result is considered in a confirmatory manner according to the approach described below. If the model fails to converge due to the complex cluster structure and variance components are estimated as zero, we will simplify the model stepwise by removing random effects.

Second primary outcome (hypothesis II): We perform a mixed logistic regression with the binary variable patient dropout after 20 weeks (yes vs no) as dependent variable, IG, therapeutic approach (CBT vs PDT) and comorbid SCID-5 personality disorder (yes vs no) as fixed effects, and cooperation centre, supervision group (if possible), and therapist as nested random effects.

The two primary hypotheses are hierarchically ordered and tested one after the other at the two-sided 5% level. Hypothesis II is only tested if hypothesis I could be rejected. If hypothesis I cannot be rejected, hypothesis II is no longer examined confirmatory but exploratory. This procedure ensures a family-wise type I error of 5%.

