These analyses will be conducted either in the full analysis set, which is as complete as possible and as close as possible to the intention-to-treat ideal of including all randomised participants,^118^ or in the sample excluding randomised participants who did not receive a single dose (ie, one therapy session). Missing values are implicitly imputed by the chosen model. This allows for a (modified) intention-to-treat analysis, which results in unbiased estimations under the missing-at-random assumption. Missing values for treatment dropout can only be due to both patient and therapist leaving the study.

Sensitivity analysis for primary endpoints: To investigate the robustness of the results of the primary analyses, we will conduct sensitivity analyses with multiple imputation by chained equations as the imputation strategy. Additionally, primary analyses are repeated in the PP sample. Definition PP sample: patients who receive therapy by trained or non-trained and accordingly supervised therapists as intended by their group allocation without protocol deviations. Protocol violations include: (a) patient’s use of non-allowed medications (eg, newly prescribed antidepressant) or not allowed concurrent psychological treatments, (b) less than 12 completed therapy sessions at the end of week 20 (not relevant with respect to the outcome therapy dropout), (c) participants belonging to the IG, but not receiving the intervention in the intended dose, (d) non-compliant completion of assessments (eg, too early or too late). It will be documented (a) whether the protocol violation occurred during or after the study therapy or overlapping and (b) the measurement time point(s) for which the protocol violation is relevant.

Secondary outcomes: Secondary outcomes are examined exploratorily with analogous methods appropriate for the scale level (ie, mixed linear, logistic, ordinal, or Poisson/negative binomial regression). The contrast of the IG versus CG at week 35 of BDI-II changes from baseline of the model of the first primary outcome is used as a result of secondary outcome analysis. Analyses will be conducted up to and including the first follow-up (week 35) and will be repeated at a later time to include the subsequent measurement points (ie, follow-ups 2 and 3).

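### The first primary model names patient as a random effect as its only within-patient term; with a constant residual variance, the week-20 standard error would rest on a variance averaged over visits

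*Protocol article*

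**What the plan says.** For hypothesis I, the Statistical analyses section of the protocol article states: "We use a linear mixed model with repeated measures with changes from baseline as dependent variable". The fixed effects are group, approach, time, personality disorder, baseline BDI-II and time by group. The random effects are cooperation centre, "supervision group (if possible), therapist (=cluster) and patient as nested random effects". No random slope, residual covariance structure or visit-specific variance is named. If the model does not converge, the only remedy given is to remove random effects stepwise. The interaction is dropped if its p value exceeds 0.15.

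On the visits used: "Measurement points up to and including the first follow-up (within the current funding period) will be considered". Table 1 (Measurement time points) lists the BDI-II at "Screening, BA, after the fifth therapy session, Post, FUP 1, 2, 3". On the target: "The contrast of the IG after 20 weeks is the result of the primary analysis". On missing data, the model is said to impute implicitly, "which results in unbiased estimations under the missing-at-random assumption". The section also says: "A statistical analysis plan that contains the details of all planned analyses will be finalised before database lock".

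**The concern.** A patient random intercept with independent, constant-variance residuals is compound symmetry: one variance for change at every visit and one correlation for every pair of visits. Change scores often do not behave like that. Sessions are weekly, so session 5 lies much nearer to baseline than week 20, and early change would naturally spread less than later change. If visit variances differ, a pooled variance gives the week-20 contrast a standard error that is too small or too large.

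This test is also the gatekeeper for dropout, which is tested confirmatorily only if hypothesis I is rejected. Likelihood-based handling of missing week-20 values borrows from the other visits through the covariance, so the missing-at-random statement relies on that covariance being adequate. The article expects 15% loss at week 20.

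**Working it through.** **The plan's own figure.** Sample size calculation: difference 4.0, SD 7.3, two-sided alpha 0.05, power 0.90, ICC 0.05, two patients per therapist.

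- n per arm = 2(1.960 + 1.282)² × 7.3² / 4.0² = 70.
- Design effect 1 + (2 − 1) × 0.05 = 1.05, so 73.5 patients, or 37 therapists per arm.
- With the noncentral t, power is 0.894 at 37 therapists and 0.902 at 38.

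The stated 38 therapists and 76 patients per arm reproduce. The SD of 7.3 is therefore used for week 20 below.

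**Inputs the article does not give.** SDs at session 5 and week 35, and correlations between visits, are assumptions.

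**Closed form.** With complete data and the interaction kept, the week-20 estimate is the difference of the two week-20 means. Its true variance is proportional to the week-20 variance, but compound symmetry estimates it from the mean of the visit variances. So r = √(mean visit variance / 7.3²), and the type I error is 2[1 − Φ(1.96 r)].

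Example, SDs 5.0/7.3/7.5: mean variance (25.00 + 53.29 + 56.25)/3 = 44.85; r = √(44.85/53.29) = 0.917; type I error 7.2%.

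| Visits in model | Assumed SDs | r | Type I error |
|---|---|---|---|
| Session 5, weeks 20, 35 | 4.0/7.3/7.3 | 0.876 | 8.6% |
| same | 4.5/7.3/7.3 | 0.891 | 8.1% |
| same | 5.0/7.3/7.5 | 0.917 | 7.2% |
| same | 6.0/7.3/7.5 | 0.954 | 6.2% |
| same | 6.0/7.3/8.5 | 1.005 | 4.9% |
| same | 4.0/7.3/10 | 1.029 | 4.4% |
| Weeks 20, 35 | 7.3/8.0 | 1.049 | 4.0% |
| same | 7.3/9.0 | 1.122 | 2.8% |
| same | 7.3/10 | 1.199 | 1.9% |

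**Simulation with therapist clusters.** 3000 null trials per pattern; 116 therapists with two patients each; ICC 0.05; 15% missing at week 20; correlations 0.6, 0.5 and 0.7; therapist and patient random intercepts; interaction kept.

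- Equal SDs and equal correlations: 4.8%.
- 6/7.3/8: 5.8%.
- 5/7.3/8.5: 6.8%.
- 4/7.3/8.5: 7.4%.
- 4/7.3/10: 5.5%.
- Weeks 20 and 35 only, 7.3/8.5: 3.0%.

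Monte Carlo error is about 0.3 to 0.5 percentage points.

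**Does an unstructured covariance cure it?** With the interaction kept, SDs 5/7.3/7.5 gave 7.1% for the random intercept and 4.8% for unstructured. Weeks 20 and 35 only, SDs 7.3/9, gave 3.0% and 5.1%. A separate run (5/7.3/7.5, 116 per arm, arm-different missing-at-random loss, 2000 trials) gave 7.7% and 5.0%. The week-20 bias there was 0.12 and 0.03 BDI-II units, against a planned effect of 4.0.

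**With the elimination rule applied.** For 5/7.3/7.5, dropping the interaction at p > 0.15 gave 6.7% for the random intercept and 7.2% for unstructured. Once the interaction is dropped, the reported contrast is a common effect over visits, so the rule chooses between two tests after seeing the data. The covariance change alone does not undo that.

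**The case against.** The strongest reply is that the article is silent, not wrong. It nowhere says that patient enters only as an intercept or that residuals are independent with constant variance. Visit-specific residual variances could accompany the patient effect, and details are deferred to an analysis plan that is not shown. A reader might infer that the plan is committed to equal variances; the text does not support that. What remains is that the article does list its within-patient term. An unstructured residual covariance cannot be identified alongside a patient random intercept, so the usual unstructured model would replace an item on that list, not merely fill a gap.

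A reader might also infer that the test is wrong whenever change spreads out over time. It is not: week 20 is the middle of three visits, and 6.0/7.3/8.5 leaves the error at 4.9%.

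A third objection is that inflation needs session 5 in the model. Table 1 lists it ("after the fifth therapy session, Post, FUP 1, 2, 3"), but early change to session 5 appears in the article under variables for subsidiary research questions, and the BDI-II endpoints are defined at week 20 and later. This stands: session-5 use is unsettled, and without it the error is conservative when week 35 is the more variable visit.

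Finally, one might read the family-wise 5% statement as false. That sentence describes the ordered testing of two hypotheses and is correct about multiplicity. It does not speak to the covariance model, though ordered testing does presume that each test holds its own level.

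The missing-data bias found is small, and multiple imputation is already planned as a sensitivity analysis.

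**Conclusion.** The point holds conditionally. Fitted with the listed random effects and a constant residual variance, and with the interaction in the model, the week-20 standard error uses a variance pooled over visits. Under the assumed SDs the type I error runs from about 4% to 8% with session 5 included (8.6% in the most extreme pattern tried). It runs from about 3% to 4% with weeks 20 and 35 only and a week-35 SD of 8 to 9, and lower still at an SD of 10. Some patterns show no distortion. These sizes rest on SDs and correlations that the article does not give, so no actual error rate is demonstrated. The case for change is that a better-behaved model is available at almost no cost for the test that opens the confirmatory sequence.

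**What to change.** In the analysis plan, before database lock:

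- Replace the patient random effect with an unstructured within-patient covariance over the post-baseline visits. Keep centre, supervision group and therapist as random effects.
- Name a fallback that still allows unequal variances, such as heterogeneous Toeplitz. Removing random effects, the only remedy now stated, cannot repair unequal variances.
- Always retain the time-by-group interaction and delete the p > 0.15 elimination rule. Otherwise the covariance change does not bring the week-20 test to 5%.
- State whether the session-5 BDI-II enters the model.

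No new data are needed. The within-patient covariance has six parameters for three visits or three for two, against two under compound symmetry: four or one extra, with 232 patients planned for analysis.

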### Hypotheses and research questions

The two hierarchically ordered primary hypotheses are: In MAFT-D compared with TAU, a stronger reduction of patient-rated depressive symptoms (first primary endpoint) and a lower rate of patient dropout (second primary endpoint) is expected from baseline to 20 weeks after baseline. The study’s hierarchical testing framework first assesses symptom reduction, followed by dropout rates. While this sequence reasonably suggests that dropout rate effects might be less relevant without significant symptom reduction, we would like to point out that one could also argue that both hypotheses hold independent value and could merit separate evaluation, given their relevance to treatment quality. While the time point (after 20 weeks) was chosen carefully to ensure comparability with other studies, it carries the risk that the intervention dose might be insufficient at this stage, with effects potentially becoming evident only at later follow-ups.

Secondary patient-related hypotheses are: In MAFT-D compared with TAU, stronger reduction of patient-rated depressive symptoms after 35 weeks, and 20 and 36 months, lower rate of dropout at week 35 and month 20 and 36, stronger reduction of observer-rated depressive symptoms, and patient-rated anxiety, somatic complaints, personality structure deficits, interpersonal problems, and quality of life after 20 and 35 weeks, and 20 and 36 months.

Secondary therapist-related hypotheses are: In MAFT-D compared with TAU, stronger increase in observer-rated interpersonal skills after 35 weeks, and therapist-rated therapeutic skills, trait-like relational manner in therapy, emotional suppression, alexithymic traits (difficulties identifying and describing feelings) and satisfaction with supervision after 20 and 35 weeks, and 20 and 36 months.

The hypotheses regarding mediators of MAFT-D effectiveness are: MAFT-D generates more favourable outcomes via an improved therapeutic alliance and increased therapist skills to deal with alliance ruptures. Corresponding mediator variables are: (1) therapeutic alliance,^52^ (2) ratio of unresolved/resolved alliance ruptures,^22^ (3) convergence of patients’ and therapists’ alliance ratings over time,^14 53 54^ (4) interventions referring to the therapeutic relationship in the here and now,^13^ (5) nondirective supportive therapist’s techniques,^55 56^ (6) therapists’ competence in session (empathy) and^57^ (7) adherence to MAFT-D.^13 22^

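### Dropping the time-by-group interaction at p>0.15 turns the primary week-20 contrast into an average over visits, and its test no longer has 5% error

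*Protocol article*

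**What the plan says.** In the protocol article, Statistical analyses, the first primary outcome is modelled as change from baseline in BDI-II. The fixed effects are group, approach, time, personality disorder and a time-by-group term, with baseline BDI-II as covariate and nested random effects. On the visits: "Measurement points up to and including the first follow-up (within the current funding period) will be considered". On the interaction: "The interaction term is eliminated from the model if the corresponding interaction p value is >0.15". On the result: "The contrast of the IG after 20 weeks is the result of the primary analysis".

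The same section says the two primary hypotheses are "tested one after the other at the two-sided 5% level" and concludes: "This procedure ensures a family-wise type I error of 5" per cent. Under secondary outcomes it takes "The contrast of the IG versus CG at week 35 of BDI-II changes from baseline of the model of the first primary outcome" as the week-35 result. The section Hypotheses and research questions says of the 20-week time point that "it carries the risk that the intervention dose might be insufficient at this stage", and that effects may show only at later follow-ups.

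**The concern.** The endpoint is the arm difference in BDI-II change at week 20. With the interaction in the model, the week-20 contrast estimates that. With the interaction removed, there is one group coefficient for all visits, so the contrasts at week 20 and week 35 are the same number. A preliminary significance test therefore decides which quantity is estimated, and the result is labelled week 20 either way.

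A p value above 0.15 does not show that the effect is constant. The sample size was set for main effects, not for an interaction, and the article itself allows that the effect may come late. If it does, averaging credits part of it to week 20. No adjustment for the selection step is stated, so neither the nominal 5% level nor the nominal 95% confidence interval is assured. This is the test on which the confirmatory status of hypothesis II depends.

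**Working it through.** **The plan's own figure.** The section on sample size gives a difference of 4.0, SD 7.3, power 0.90, two-sided 5%, ICC 0.05 and 2 patients per therapist. The simple formula gives 2 × (1.960 + 1.282)² × 7.3² / 4.0² = 70 per arm. The design effect is 1 + (2 − 1) × 0.05 = 1.05, and 70 × 1.05 = 73.5. The t-based cluster version gives 38 therapists, or 76 patients, per arm, as stated. The sample size is not in question; the stated 5% error rate is.

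**Inputs.** With 240 patients enrolled and 15% loss at post-assessment, each arm has 120 × 0.85 = 102. The standard error of the arm difference at one visit is SE = 7.3 × √(2 × 1.05 / 102) = 1.047. The correlation r between the week-20 and week-35 arm differences is not in the article and is varied. Variances are taken as equal and tests as large-sample normal.

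**The rule for two visits (weeks 20 and 35).** Let D be the week-35 minus the week-20 estimate and A their mean.

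- SE(D) = SE × √(2(1 − r)) and SE(A) = SE × √((1 + r)/2). With equal variances D and A are independent.
- If |D|/SE(D) < 1.440 (p > 0.15), the interaction is dropped and A is tested against 1.96 × SE(A).
- Otherwise the week-20 estimate is tested against 1.96 × SE.

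**Worked case, r = 0.5.** SE(D) = 1.047 and SE(A) = 0.907.

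- *No effect at either visit.* The term is dropped in 85% of trials, which contributes 0.85 × 5% = 4.25%. The other 15% contribute 1.90%: they were selected for a large difference between visits, so the week-20 test rejects in 1.90/15 = 12.7% of them. The total is 6.15%.
- *Week-20 effect 0, week-35 effect 1.8.* The term is dropped with probability Φ(−0.279) − Φ(−3.158) = 0.389. In that branch A has mean 0.9, and 0.9/0.907 = 0.992, so rejection is Φ(−0.968) + Φ(−2.952) = 0.168. The contribution is 0.389 × 0.168 = 6.5%. The branch that keeps the term adds 2.8%. The total is 9.3%.

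**Results by numerical integration, 102 per arm**

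| | r = 0.3 | r = 0.5 | r = 0.65 | r = 0.8 |
|---|---|---|---|---|
| Type I error, no effect at either visit | 6.6% | 6.2% | 5.8% | 5.5% |
| Peak type I error, week-20 effect 0 | 12.2% | 9.3% | 7.7% | 6.4% |
| Week-35 effect at the peak (points) | 2.15 | 1.8 | 1.5 | 1.1 |
| Type I error, effects 0 and 4 | 6.6% | 5.3% | 5.0% | 5.0% |
| Coverage of the 95% interval for week 20, effects 2 and 4 | 87.9% | 90.8% | 92.8% | 94.5% |

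With the interaction always kept, every type I error is 5.0% and coverage is 95%. Simulation with 2,000,000 draws agrees.

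**Size of the shift.** With effects 2 at week 20 and 4 at week 35, A has mean 3. Whenever the term is dropped, the figure reported for week 20 is too large by 1.0 point on average, a quarter of the planned 4.0.

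**Three visits.** Table 1 lists the BDI-II at "Screening, BA, after the fifth therapy session, Post, FUP 1, 2, 3". If the fifth-session value also enters the model, the type I error at r = 0.5 is 6.1% with no effect anywhere. It is 7.3% with an effect of 2.0 at week 35 only (116 per arm).

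**The case against.** The strongest reply is that the excess is modest and the larger figures rest on inputs the article does not give. If there is no effect at any visit, the error is 5.5% to 6.2% for r between 0.8 and 0.5. The 9.3% peak needs r = 0.5, exactly no effect at week 20 and about 1.8 points at week 35. A late effect as large as the planned 4.0 points brings the error back to 5.0% to 5.3%. Coverage is close to nominal at r = 0.8. The shared therapist effect raises the correlation slightly, (0.5 + 0.05)/1.05 = 0.52, which lowers the worst case to about 9.1%. In that worst case there is a true benefit at week 35, so the error is about timing. All this stands and limits the size of the error-rate problem.

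Three further points also stand. The fifth-session BDI-II is listed under the subsidiary research questions, so two visits is the more natural reading of the primary model. Hypothesis II keeps its own 5% test, so the family-wise excess is the excess of hypothesis I and nothing more. The article's remark about late effects covers all later follow-ups and does not single out week 35.

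The rule is also fixed in advance with a numeric threshold, which removes analyst discretion. That does not help: prespecifying a data-dependent choice of estimand does not restore the 5% level. None of these points touches the change of estimand, which follows from the model at any correlation.

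**Conclusion.** The concern holds. As written, the rule makes the confirmatory week-20 result a common effect over visits whenever the interaction p value exceeds 0.15, and the primary and week-35 results then coincide. That branch is taken in 85% of trials if the effect is constant over time. This part needs no assumption about the data.

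The claim of 5% family-wise error is also not met. For r from 0.5 to 0.8, the excess is about 0.5 to 1.2 percentage points with no effect at either visit. At its peak, with a modest effect at week 35 only, it is 1.4 to 4.3 points. These sizes assume two visits, equal variances, normal tests and 102 patients per arm. Unequal variances or missing data would change the weights of the average but not the conclusion. Because this is the first confirmatory test and the repair is simple, it should be corrected before the analysis plan is finalised.

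**What to change.** Delete the elimination sentence. Keep the time-by-group interaction in the model whatever its p value, with time as a categorical factor. Take the week-20 contrast (primary) and the week-35 contrast (secondary) from that single model. Name the visits that enter the model, so that it is clear whether the fifth-session BDI-II is among them. If an average effect over visits is of interest, define it as a separate secondary contrast.

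The article says the statistical analysis plan will be finalised before database lock, so the change can be made there and in a protocol amendment. Recruitment, data collection and sample size are unaffected. The cost is a little precision when the effect really is constant: at 4.0 points and 102 per arm, power is 96.8% with the interaction kept, against 97.6% (r = 0.8) to 98.3% (r = 0.5) under the present rule.

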### Methods against bias

Randomisation and stratification: Therapists are randomly assigned by a 1:1 ratio to receive MAFT-D versus TAU stratified by study centre and approach (CBT/PDT). Patients are randomly assigned to MAFT-D versus TAU stratified by study centre, subsequently by approach (CBT/PDT), and comorbid personality disorder (SCID-5-PD, yes vs no). Since it emerged that each cooperating centre offers training in only one therapeutic approach, stratification by therapeutic approach proved to be practically redundant. Block randomisation with variable block length is used. Patients are assigned to therapists appropriate to the random group. Randomisations will be performed centrally by [name] group, University Medical Center Hamburg Eppendorf. Allocation is done via the electronic case report forms (eCRF) (implemented in secuTrial).

Blinding: Therapists will be aware of allocation, patients will be blinded. Interviewers, raters and persons conducting the statistical analyses will be blinded. There will be strictly separate role assignments in the study team (raters/interviewers vs unblinded study team members). Raters/interviewers will work physically separated from unblinded staff.

Allegiance bias: Principal investigator (PI), research group members and national or international collaborators are PDT, CBT or systemic therapists, recruiting centres are from both therapeutic approaches, statisticians have no affiliation to a therapeutic approach.

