### Sample size calculation, number of study participants

Depressive symptoms: There are no prior studies that closely align with our study in terms of study population, intervention and measurement instruments. In our view, the chosen reference Bambling *et al*^45^) represents the best available compromise, as it examines a population of depressed patients, employs an alliance-focused supervision approach and uses the BDI-II as a measurement instrument. Accordingly, we assume a higher reduction in BDIII after 20 weeks in MAFT-D compared with TAU of 4.0 BDI-II units with a SD of 7.3 BDI-II units. To detect such an effect with a type I error of .05 (two-sided hypothesis), a power of .90, an intracluster correlation coefficient of 0.05, and a cluster size of 2 patients per therapist on average, we need 76 therapists and 152 patients in total (38 therapists and 76 patients per group, PASS 15, tests for two means in a cluster-randomised design).

Treatment dropout: We expect that MAFT-D will reduce the treatment dropout rate after 20 weeks from 30% to 12.5%, corresponding to an OR of 3.0. The expected dropout rate of 30% for TAU is a conservative estimate based on a recent meta-analysis (35% dropout)^7^ and numbers in our own clinic (n=3.357 depressed patients; 33% dropout). Previous studies on different AFT approaches reported a difference in treatment dropout rates of 17.5% or greater (Bambling *et al*: IG1=6.1%, IG2=3%, CG=35%; Constantino *et al*: IG=0%, CG=27.3%; Muran *et al*: IG=20%, CG1=37%, CG2=46%).^45 46 76^ With identical design effects, 58 therapists and 116 patients per group (116 therapists, 232 patients in total) are needed to detect this difference (PASS 15, test for two proportions in a cluster-randomised design). We expect that 3% of the randomised sample are not part of the full analysis set (oriented on numbers from the trial of Schramm *et al*^77^) due to the lack of any data postrandomisation.^78^ Thus, based on the larger sample size required for dropout, a sample of 120 therapists and 240 patients in total has to be enrolled.

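### The dropout model leaves out baseline BDI-II, a covariate the trial already collects; prespecifying it would be a small, nearly free gain on the endpoint that sets the sample size

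*Protocol article*

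**What the plan says.** Under Statistical analyses, the Protocol article gives the terms of both primary models. The model for BDI-II change includes "baseline BDI-II score as covariate, time by IG interaction". The mixed logistic model for dropout at 20 weeks has "IG, therapeutic approach (CBT vs PDT) and comorbid SCID-5 personality disorder (yes vs no) as fixed effects, and cooperation centre, supervision group" and therapist, the last three as nested random effects. It has no severity term.

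Baseline BDI-II is available. A score of at least 20 is an entry criterion, and Table 1 schedules the BDI-II at screening and again at baseline.

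Under Sample size calculation, the plan expects MAFT-D to "reduce the treatment dropout rate after 20 weeks from 30% to 12.5%, corresponding to an OR of 3.0", and concludes that "58 therapists and 116 patients per group (116 therapists, 232 patients in total) are needed to detect this difference". This is the larger of the two requirements, so it fixes the enrolment of 240 patients. The BDI-II endpoint needs only 152.

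**The concern.** Baseline severity is a plausible predictor of who leaves therapy. The article itself puts depression severity first among the baseline characteristics it would compare between CBT and PDT and, if they differ, adjust for when testing whether the intervention works equally in both. Randomisation is stratified by centre (hence approach) and personality disorder, not by severity. Chance imbalance in severity between the arms is therefore left unadjusted in the dropout analysis.

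If severity does predict dropout, adjusting for it raises the power of the group test. The covariate is used where power is ample and left out where power is only just met. At stake is a small amount of power on the second primary endpoint, and some precision if the effect is also reported as a risk difference.

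**Working it through.** **1. Reproduce the planned sample size without a covariate.**

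Inputs from Sample size calculation: dropout 30% vs 12.5%; a two-sided 5% level with 90% power; and, for the clustering, "an intracluster correlation coefficient of 0.05, and a cluster size of 2 patients per therapist on average". The power and clustering values are stated for BDI-II and are taken to apply to dropout as well. Allocation is 1:1 (Methods against bias).

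- Odds ratio: (0.30/0.70) / (0.125/0.875) = 3.0, as stated.
- Design effect: 1 + (2 − 1) × 0.05 = 1.05.
- Unpooled formula: n = (1.960 + 1.282)² × (0.30 × 0.70 + 0.125 × 0.875) / 0.175² = 109.58 per group.
- With clustering: 109.58 × 1.05 = 115.06, rounded up to 58 therapists with 2 patients each = 116 per group. This matches the plan.
- Allowance for 3% outside the full analysis set: 232 / 0.97 = 239.2, so 240. This also matches.

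**2. Power in hand.**

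- Dropout, 116 per group: 90.2% (unpooled variance) or 89.4% (pooled).
- BDI-II, 4.0 points with SD 7.3, after the assumed 15% loss (232 × 0.85 / 2 = 98.6 per group): 96.4%.

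**3. Effect of adding the covariate.**

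The article gives no association between baseline BDI-II and dropout, so a range is assumed. Logistic regression was simulated with 116 / 1.05 ≈ 110 effective patients per arm, marginal dropout held at 30% and 12.5%, a standardised baseline covariate, and 20,000 trials per row:

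| Assumed OR per SD | Power without | Power with | Median SE of log OR, without → with |
|---|---|---|---|
| 1.0 | 89.6% | 89.6% | 0.358 → 0.359 |
| 1.2 | 89.4% | 89.5% | 0.358 → 0.361 |
| 1.35 | 89.8% | 90.0% | 0.358 → 0.363 |
| 1.5 | 89.5% | 90.1% | 0.358 → 0.365 |
| 2.0 | 89.9% | 91.9% | 0.358 → 0.376 |

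The Monte Carlo standard error of each power figure is √(0.9 × 0.1 / 20,000) ≈ 0.2 points. A separate simulation with a truncated severity distribution (8,000 trials per scenario) gave about 0 points at 1.0 to 1.2, 0.8 at 1.5 and 2.2 at 2.0.

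The standard error of the log odds ratio rises in every row. Power still rises when there is an association, because the conditional log odds ratio lies further from zero than the marginal one.

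**4. Standardised risk difference.**

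On this scale precision does improve. The variance fell by about 2% at an odds ratio of 1.5 per SD and by about 6% to 7% at 2.0. It rose by about 0.6% when there was no association.

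**5. Room for the term.**

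Expected events: 0.30 × 116 + 0.125 × 116 = 34.8 + 14.5 = 49.3. One further fixed effect is affordable.

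The simulations represent clustering by the design effect and do not fit the random effects.

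**The case against.** The best defence is that the dropout model is coherent as written. It adjusts for the stratification factors: personality disorder and approach as fixed effects, centre as a random effect. The first model's use of BDI-II sets no precedent, because there it is the baseline value of the outcome and dropout has no baseline value. No section says that severity predicts dropout; predictors of dropout are listed as an open subsidiary question. The entry threshold of 20 narrows the BDI-II range, which makes the weaker associations more likely. All of this stands, and it keeps the point small. It does not show a cost to adding the term.

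A reader might go further in four ways that the article does not support:

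- **That the treatment odds ratio is estimated less precisely than it could be.** In a logistic model the standard error of the log odds ratio goes up with adjustment, as the table shows.
- **That the trial is underpowered without the covariate.** The planned numbers reproduce exactly from unadjusted proportions.
- **That the two primary models are inconsistent, or the comparison is biased.** Randomisation protects the comparison, and the different role of BDI-II explains the difference between the models.
- **That the covariate is needed to make missing dropout status ignorable.** Patients who cannot be reached are classed as dropouts, status is missing only if patient and therapist both leave the study, and multiple imputation is already planned as a sensitivity analysis. Little is left for the covariate to repair.

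The unseen analysis plan may hold more detail. However, the article already names the model's terms, so the choice is open to comment.

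**Conclusion.** The point holds as an optional improvement, not as an error. The dropout model omits a baseline score that the trial already has, on the endpoint with the least power to spare. The likely benefit runs from nothing to about 2 points of power over an assumed odds ratio per SD of 1.0 to 2.0.

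In patients, the saving is 1 − [(1.96 + z of power without) / (1.96 + z of power with)]². At 1.5 this is 1 − (3.211 / 3.244)² ≈ 2%, or about 5 of 232. At 2.0 it is 1 − (3.237 / 3.358)² ≈ 7%, or about 16 to 17 of 232.

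The size rests wholly on the assumed association. The absence of a material loss when there is none does not. Hypothesis II is confirmatory only if hypothesis I is rejected, which further limits what is at stake. Priority is low.

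**What to change.** Before database lock, state in the analysis plan that the mixed logistic model for dropout includes baseline BDI-II as a continuous fixed effect, using the same baseline value as the first primary model. Report the standardised risk difference beside the conditional odds ratio; this is the scale on which adjustment can improve precision.

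The cost is one model term and one extra reported estimate. No new data and no change to the sample size are needed. The odds ratio becomes conditional on one more covariate, in a model that is already conditional on approach, personality disorder and the random effects. Fixing the term now also avoids a data-dependent decision to add it later.
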